| Number of Participants with Rationale                                 | Postoperative wound problems occur in at least 5% percent of all interventions. Incidence for both, revision surgery and/or SSI, in our selected patient population is set for 10%. We perform a superiority RCT with a power of 80% in favor of the decolonization. With event-free surgeries to 95% in the decolonization arm versus 90% in the standard arm, we formally need 2 x 474 surgery episodes, which we sum up to 2 x 500 surgeries (n = 1'000). A patient can be included several times as long as he/she gets not infected.

At the Balgrist, we perform at least 5000 surgical operations per year (in reality more than 6000). With a very conservative estimation, we see at least 600 surgical episodes per year (12% of surgeries) that can be included; mostly because of the advanced age, diabetes, and high ASA-Scores of our patients. The interventional part of the trial lasts two years; with interim analysis after 1 year (+/- 2 months). An independent advisory board might stop the trial. For the secondary outcomes (adverse events, questionnaire), we do not require a minimal sample size. |                            |                            |          |          |             |          |          |          |                              |              |                            |                            |                     |       |       |   |               |       |       |       |                          |        |        |        |                      |       |       |       |                  |       |     |       |                           |               |               |               |

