### 6.2.1 Method of assignment to treatment/intervention (randomization, stratification)

After written informed consent given participants will be randomized with a 1:1 ratio in either treatment group. Randomization is done by designated study staff drawing a sealed envelope containing a randomization card or electronically. Patients are informed about the assignment by the investigators.

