### **11.2 Determination of Sample Size**

In our hospital, postoperative wound problems occur in at least 5% percent of all interventions. Incidence for both, revision surgery and/or SSI, in our selected patient population is set for 10% according to our clinical experience among the selected patient population that composes our study population.

We perform a superiority RCT with a power of 80% in favor of the decolonization. With 95% event-free surgeries in the decolonization arm versus 90% in the standard arm, we formally need 2 x 474 orthopedic surgery episodes, which we sum up to 2 x 500 surgeries (n = 1'000). A patient can be included several times as long as he/she gets not infected and has not witnessed postoperative wound problems.

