### 11.3 Planned Analyses

All analyses will be performed for the entire study population. In a second step, all analyses will be separately performed according to subgroups of patients, based on the type of orthopaedic surgical procedure (e.g. arthroplasties, implant-related surgeries, etc.). We will use descriptive statistics and will perform group comparisons (using the Pearson- $\chi^2$ -test, the Fischer-exact-test, or the Wilcoxon-ranksum-test), as appropriate. We will also perform composite (SSI and wound problems) and separate (SSI or wound problems) multivariate analysis using a Cox regression model targeting the co-primary outcome variables. For the primary outcome parameter, univariable and multivariable results will be computed using a Cox regression analysis. Variables with a  $p$  value  $\leq 0.2$  in univariate analysis will be included in a stepwise forward selection process for multivariate analysis. Key variables will be checked for co-linearity and interaction. The number of variables in the final model is limited to the ratio of 1 variable to 5 to 8 outcome events. The significance level is  $p \leq 0.05$  (two-tailed).

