#### 11.3.1 Interim analysis and early termination

We will perform one interim analysis one year (+/- 2 months) after the inclusion of the first patient. If group comparison between the decolonization and non-decolonization arms are striking and statistically significant in terms of any study objectives, the independent Data Monitoring committee will decide upon the interruption and early termination of the trial. Otherwise, the study continues. Of note, the Data Monitoring committee has the right to call on a premature, additional interim analysis.

If the crude group comparison analysis is not sufficiently meaningful, we will perform a futility analysis to check if the expected statistical power for the final analysis will not be  $< 30\%$  and therefore unacceptable. If it is lower than  $30\%$ , we will consider the trial will not be able to demonstrate the result, and the recruitment will be no more ethical. The most frequent conditional power evaluated under the current trend (i.e. using the information from the collected data) will be assessed. It was demonstrated that futility analyses decrease the statistical power of the final analysis in superiority trials, but in our knowledge, this topic was not explored for non-inferiority trials. To balance (at least partially) this loss of power, we may recruit 100 supplementary patients per arm. E.g. approximately 600 episodes in each randomization arm.

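### Section 11.3.1 leaves the final size open, at 500 or about 600 per arm, through an option the investigators may use after a by-arm interim analysis

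*Protocol*

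**What the plan says.** Section 11.2 gives the planned size: "we formally need 2 x 474 orthopedic surgery episodes, which we sum up to 2 x 500 surgeries (n = 1'000", based on "With 95% event-free surgeries in the decolonization arm versus 90% in the standard arm" and 80% power.

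Section 11.3.1 plans one interim analysis one year (+/- 2 months) after the first inclusion. The independent committee decides on early termination. If the crude comparison is not sufficiently meaningful, a futility analysis follows, written in the first person plural, with a 30% threshold: "The most frequent conditional power evaluated under the current trend (i.e. using the information from the collected data) will be assessed". The paragraph then notes that futility analyses cost power and continues: "To balance (at least partially) this loss of power, we may recruit 100 supplementary patients per arm", for example about 600 episodes per arm.

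Section 11.3 sets a single level: "The significance level is $p \leq 0.05$ (two-tailed". Nothing ties it to a change of sample size.

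On timing, Section 1.6 refers to interim analyses after about one and two years, and Section 10.1.3 (periodic reporting) to an annual futility analysis. Section 1.3 assigns the statistical analyses to the investigators.

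On resources, the synopsis (number of participants) states: "With a very conservative estimation, we see at least 600 surgical episodes per year (12% of surgeries) that can be included". Section 6.1.3 allows 24 months. Section 14.1 supplies 550 sets, 500 for the study and 50 in reserve.

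**The concern.** Conditional power under the current trend cannot be computed without the difference between arms. Whoever does the futility analysis therefore knows the trend, and the same paragraph, in the same first person, offers 100 more per arm. The early-stopping decision goes to the independent committee; the extension is not assigned to it.

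A final size chosen in the light of the treatment difference, followed by an ordinary 0.05 test, does not in general keep the error rate at 5%. Even where the inflation is small, a reader of the final report could not tell whether stopping at 500 or at 600 was the plan or a response to the data. The enlarged size also has to fit the supply and recruitment figures stated elsewhere in the protocol.

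**Working it through.** **1. The plan's own figure.** Inputs from Section 11.2 (10% v 5%, 80% power), Section 11.3 (two-sided 0.05) and Section 6.2.1 (1:1).

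n0 = [1.96·√(2·0.075·0.925) + 0.8416·√(0.10·0.90 + 0.05·0.95)]² / 0.05² = 434.4, i.e. 435 per arm.

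With continuity correction: n = (n0/4)·[1 + √(1 + 4/(n0·0.05))]² = 473.6, i.e. 474. This matches the protocol.

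Power with the correction is 0.823 at 500 per arm and 0.890 at 600 (0.852 and 0.909 without it).

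**2. Worst case for a choice made at an interim.** Let z be the interim statistic at n1 per arm, N the final size and t = n1/N. Under the null, the chance of rejecting at the end, given z, is

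R_N(z) = Φ[−(1.96 − √t·z)/√(1−t)] + Φ[(−1.96 − √t·z)/√(1−t)].

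The upper bound is the mean, over z ~ N(0,1), of the larger of R_500 and R_600, with no stopping:

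| n1 per arm | information (of 500) | type I error, at most |
|---|---|---|
| 150 | 30% | 5.25% |
| 200 | 40% | 5.32% |
| 250 | 50% | 5.39% |
| 400 | 80% | 5.7% |
| 450 | 90% | 5.9% |

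The information at one year is an assumption. The protocol fixes calendar time only, and 30-50% is taken as the plausible range. If N were 600 whatever the trend, the error would be 5.0%.

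**3. Choice made once the 500-per-arm result is known.** The statistics at 500 and 600 per arm correlate at √(500/600) = 0.913. The error is 1 − P(|Z500| < 1.96 and |Z600| < 1.96) = 6.91%.

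**4. The same choice with the futility stop obeyed.** Stop if Φ[(|z|/√t − 1.96)/√(1−t)] < 0.30, with t = n1/500 and no stopping for benefit.

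| information | no extension | worst-case extension |
|---|---|---|
| 30% | 3.53% | 3.54% |
| 50% | 3.80% | 3.82% |
| 80% | 4.24% | 4.27% |

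The option then adds 0.01 to 0.03 percentage points. If conditional power is instead judged at 600 per arm (t = n1/600 in the stopping rule), the 50% figure becomes 4.07%.

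Adding a stop for benefit at an unadjusted 0.05 gives 7.11% without and 7.13% with the extension at half information. That excess comes from early stopping, which is a separate matter.

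**5. Supply and recruitment.**
- Sets: 600 decolonization episodes at one set each, against 550 supplied, leaves 50 short.
- Episodes, stated minimum: 600 × 2 years = 1,200. The enlarged trial needs 2 × 600 = 1,200, or 100%; the planned one needs 1,000/1,200 = 83%.
- Episodes, higher volume: the synopsis also mentions more than 6,000 operations a year. 12% × 6,000 × 2 = 1,440, and 1,200/1,440 = 83%.

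**The case against.** **The increase may be a planning allowance.** The reason given is the general power cost of a futility look, which is known before any data. On that reading N is 600 regardless of the trend and the error is 5.0%. The text does not say that the decision follows the interim. This stands as a possible reading, but optional wording with no rule or date leaves the post-interim choice equally open.

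**The inflation disappears under the protocol's own rule.** Step 4 bears this out for a strictly enforced 30% stop at one year. But enforcement is not assured, the text does not say whether conditional power refers to 500 or 600 per arm, and no deadline confines the choice to the one-year look. Sections 1.6 and 10.1.3 mention later looks, though neither mentions sample size.

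**Stronger readings that the documents do not support.**
- *That an interim just short of significance is where the option inflates most.* At half information the reverse holds: beyond |z| of about 1.33 (p below about 0.18), extending lowers the null chance of rejection. The statement is true only of a decision made at the 500-per-arm result.
- *That the increase cannot restore power.* A size of 600 fixed in advance does. With an interim at 250 per arm and the 30% stop, power at 10% v 5% is about 0.78 with 500 and 0.83 with 600.
- *That recruitment could not reach 1,200.* The 600 a year is a stated minimum, described as very conservative.

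**The decision rule could sit in an analysis plan or charter.** It could. But the protocol does not merely omit it: it states an optional size that differs from Section 11.2 and from its own set supply.

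**Conclusion.** The point holds as an unfixed final sample size, with a modest and conditional effect on type I error. The protocol permits either 500 or about 600 per arm, chosen by people who may know the trend, and tests at an unadjusted two-sided 0.05.

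The error rates are upper bounds for this option alone: about 5.3-5.4% at 30-50% information if the futility stop is not enforced, and up to about 6.9% if the choice waits for the 500-per-arm result. The effect is negligible if the stop is strictly followed at one year with conditional power judged at 500. A reader might infer that the final test is certainly inflated; the documents show only that inflation is not prevented.

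The conflict with 550 sets needs only the assumption of one set per episode. The recruitment point is weaker: the enlarged trial takes all of the stated minimum pool, or 83% if 12% of 6,000 operations applies. The change should be made, chiefly so that the planned end of the trial is unambiguous.

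**What to change.** Before the interim, amend Section 11.3.1 in one of two ways:

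1. Fix one final size: 500 per arm with the option deleted, or 600 per arm with Section 11.2, the set supply and the timetable brought into line.
2. Allow an increase only by a rule written in advance that uses the pooled, arm-blind event rate, with a latest date for applying it.

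In either case, state that nobody who has seen interim results by arm decides the final size, and state the final size at which conditional power is evaluated.

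The cost is a few sentences in one amendment. Keeping 500 gives up a discretionary extension. Choosing 600 needs at least 50 more sets, more if a reserve is kept, and a check that 24 months is enough.

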#### 11.3.2 Final analyses

The intent-to-treat (ITT) population will consist of all randomized patients. Patients will be analysed according to treatment group assignment. Patient disposition and baseline characteristics will be based on the ITT population.

The per-protocol (PP) population will consist of all randomized patients who complete the study (or who are otherwise defined as a treatment failure) according to the clinical investigation plan and who have not deviated significantly from the protocol. All efficacy analyses will be repeated using the PP population. Any analysis involving microbiological assessments will exclude patients without an assigned baseline pathogen.

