### 9. STUDY ASSESSMENTS

#### 9.1 Assessment of primary outcome

Judged by local wound healing (healed vs delayed wound healing according to Reference). The wound healing will be assessed visually by orthopaedic surgeons. Wound nurses and the study investigators may help in the assessment of wound problems, but in case of doubtful cases, the opinion of the treating physician will dominate the decision upon the presence or absence of wound problems and/or infection.

Persistent postsurgical pain, serum laboratory markers, or the patient's subjective wound feelings will not serve as objective criteria for wound healing (or in the contrary, wound discharge and dehiscence). A wound problem solely due to stitches and localized suture problems will not count as a wound problem. A keloid or altered pigment features will not be counted as a problem in this trial. Remission is defined as the absence of any problems and as the absence of any clinical signs of infection.

The primary outcome will be assessed on both, the Intention-to-treat and the per-protocol populations.

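### The per-protocol set keeps failures whether or not they complete but event-free patients only if they complete, so membership depends on the outcome

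*Protocol*

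**What the plan says.** Section 11.3.2 defines the PP population as "all randomized patients who complete the study (or who are otherwise defined as a treatment failure", with a second condition that applies to completers and failures alike: "and who have not deviated significantly from the protocol". Treatment failure is not defined there or elsewhere in the protocol. The same section adds that "All efficacy analyses will be repeated using the PP population", and section 9.1 states that "The primary outcome will be assessed on both, the Intention-to-treat and the per-protocol populations".

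On the analysis method, section 11.3 says that for the primary outcome "univariable and multivariable results will be computed using a Cox regression analysis". It also plans chi-square and Fisher tests for group comparisons.

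Four other places bear on who completes:
- Sections 9.2 and 10.1 set follow-up at about 6 weeks, or 1 year with an implant. The 1-year contact may be by telephone.
- Section 9.2.3 expects little dropout because the visits are routine care. No rate is given.
- Section 9.2.5 terminates some patients early, including those still on antibiotics after the end-of-treatment visit.
- Section 11.4 turns missing outcome data, and missing decolonization data, into dropout from the study.

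**The concern.** Take two patients without a protocol deviation who both stop attending at month 4 after implant surgery. One had a wound revision at week 3; the other was event-free when last seen. The first is in the PP set and the second is not, and the only difference between them is the outcome. Partial follow-up is kept when it contains an event and deleted when it does not.

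Two consequences follow. PP event proportions rise, and so does their difference, which is the scale on which section 11.1 states the hypothesis. If event-free completion also differs by arm, the deletion is unequal and shifts the treatment comparison itself. The trial is unblinded and the arms carry different tasks, so unequal completion is possible.

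For the Cox model the deletion is unnecessary, because event-free partial follow-up can enter as censored time.

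**Working it through.** **Inputs from the protocol.** Section 11.2: "With 95% event-free surgeries in the decolonization arm versus 90% in the standard arm", that is, event risks of 5% and 10%; power 80%; 474 episodes per arm, raised to 500. Section 11.3: two-sided 5% level. Section 6.2.1: 1:1 allocation.

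**Plan's own figure.** With mean risk 0.075 and difference 0.05:

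n0 = [1.960·√(2·0.075·0.925) + 0.842·√(0.10·0.90 + 0.05·0.95)]² / 0.05² = 434.4, or 435 per arm.

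With continuity correction: (434.4/4)·[1 + √(1 + 4/(434.4·0.05))]² = 473.6, or 474. The stated size is reproduced, and this point does not change it.

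**Formula.** Let p be the true event risk, c the completion among event-free patients, and f the share of failures kept. If dropout is unrelated to prognosis:

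PP rate = p·f / (p·f + (1−p)·c), so PP odds = true odds × f/c.

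The protocol gives neither c nor f. Setting f = 1 (every failure occurs, and is recorded, before the patient would have left) gives an upper bound.

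**Equal completion, true 10% vs 5%, f = 1**

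| Completion, both arms | Control | Decolonization | Difference (points) | Odds ratio |
|---|---|---|---|---|
| 98% | 10.2% | 5.1% | 5.1 | 0.474 |
| 95% | 10.5% | 5.2% | 5.2 | 0.474 |
| 90% | 11.0% | 5.5% | 5.5 | 0.474 |
| 80% | 12.2% | 6.2% | 6.0 | 0.474 |

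For example, at 90%: 0.10/(0.10 + 0.90·0.90) = 0.110 and 0.05/(0.05 + 0.95·0.90) = 0.055. The odds ratio keeps its true value because f/c cancels between arms. Only the absolute scale moves.

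**Unequal completion, no true effect (10% in both arms), 500 randomized per arm, f = 1**

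| Completion, worse vs better arm | PP rates | Odds ratio (better/worse) | False significance for better arm (nominal 2.5%) |
|---|---|---|---|
| 90% vs 95% | 11.0% vs 10.5% | 0.947 | 4.4% |
| 85% vs 95% | 11.6% vs 10.5% | 0.895 | 7.6% |
| 80% vs 95% | 12.2% vs 10.5% | 0.842 | 12.6% |

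For the middle row, 0.10/(0.10 + 0.90·0.85) = 0.1156 on 500·0.865 = 432.5 episodes, and 0.10/(0.10 + 0.90·0.95) = 0.1047 on 477.5. The difference is 0.0109, with standard error 0.0208 under both the pooled and the unpooled variance. Probability = Φ[(0.0109 − 1.96·0.0208)/0.0208] = 7.6%.

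**Relaxing the upper bound.** If only half of the would-be dropouts' failures occur before they leave, f = 1 − (1−c)/2, which is 0.925 at c = 0.85 and 0.975 at c = 0.95. The PP rates become 10.8% vs 10.2%, the odds ratio 0.94, and false significance about 4.6%. If dropout always precedes failure, then f = c and the distortion disappears.

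**Does it carry over to Cox regression?** The figures above come from a two-proportion test. A simulation of the no-effect case at 85% vs 95%, with some failures falling after dropout and so unseen, gives a hazard ratio of about 0.94 under the PP rule. Keeping the same patients as censored gives 1.00.

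**The case against.** The best case for leaving the text alone has five parts.

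- **PP is a repeat analysis.** The ITT population in section 11.3.2 is all randomized patients, and efficacy analyses are repeated on PP. Nothing makes PP decisive in this superiority trial. This stands, and it limits the importance of the point. Section 9.1 does, however, name both sets for the primary outcome without ranking them.
- **Dropout may be small.** Section 9.2.3 expects this, and a telephone contact at 1 year makes completion easy. This also stands: at 98% completion the rates move by only 0.1 to 0.2 points. Nothing in the protocol supports a particular gap between arms.
- **A completer set has some use for simple proportions.** That is fair for the chi-square and Fisher comparisons, but it does not justify keeping non-completers with an event while removing those without.
- **Retaining failures is proper.** Agreed. Dropping failures who were terminated early under section 9.2.5 would bias in the opposite direction. The fault lies in excluding event-free partial follow-up.
- **Editing section 11.3.2 alone is not enough.** Also agreed: the dropout rule in section 11.4 could still remove the same patients.

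A reader might infer three stronger things, none of which the document supports. The set does not keep every failure, since failures with significant deviations are excluded too. The rule does not by itself bias the relative comparison; equal completion leaves the odds ratio unchanged. Nor does it build in a false benefit for decolonization. The one arm-specific trigger in the text, missing decolonization data in section 11.4, could lower completion in the decolonization arm, since controls have neither the set nor the questionnaire (section 8.1.2). That would work against decolonization.

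**Conclusion.** The point holds: PP membership depends on the outcome. Absolute PP rates and their difference are inflated whenever some failures precede would-be dropout. The relative effect is biased only when event-free completion differs by arm, and then in either direction.

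The size ranges from negligible, at completion near 98% in both arms, to a one-sided false-significance rate between about 4.6% and 7.6% at 85% vs 95%. All of this rests on assumed completion rates, on dropout unrelated to prognosis, and on when failures occur relative to dropout. The protocol fixes none of these.

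It is a defect in a stated definition that deserves correction because it is so cheap to remove. It does not threaten the ITT analysis or the sample size.

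**What to change.** In section 11.3.2, define the PP population as all randomized episodes without a major protocol deviation, judged without knowledge of the outcome, and with no completion requirement. State that failures, including those terminated early, count as events, and that event-free episodes not reaching the last visit are censored at their last outcome assessment in the Cox model. Remove the treatment-failure clause, which then has no function.

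In section 11.4, amend the missing-data rule so that incomplete outcome follow-up leads to censoring rather than removal from the analysis.

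With dropout unrelated to prognosis, this returns the expected rates to 10% and 5% and the two-sided error under no effect to 5%. The cost is wording in two sections, with no extra data and no change to the 474 per arm. The one downside is that absolute PP rates must be read from time-to-event estimates rather than from simple proportions.
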